### Framework

We adopt a superiority hypothesis testing framework for this trial, examining whether combining T2D genetic risk communication with theory-based wearable device functions will lead to significant increases in objectively measured MVPA time and whether such changes will be sustained at the 6-month postintervention follow-up. Each intervention group (intervention arm 1 and intervention arm 2) will be compared separately with the control group and with each other.

### Interim Analysis and Stopping Guidance

No interim analysis is planned for this study, as the intervention is not expected to cause harm to participants or raise safety concerns that would warrant ending the trial prematurely.

### Ethical Considerations

This study was reviewed and approved by the institutional review board of the University of Hong Kong (HKU) and Hospital Authority Hong Kong West Cluster on December 8, 2022 (UW 22-007).

A subject information sheet and a written informed consent form were provided to each study participant before any assessment or data collection. Participants were given sufficient time to read through both documents and the opportunity to ask questions. The consent form included a section asking whether participants agreed to allow the data from this study to be used in future ancillary research. Participants were informed that they could withdraw from the study at any stage without providing a reason.

All study materials and records are stored securely at the study site. All electronic participant records and responses are maintained on the network drives of the HKU research laboratory. Hard copies of study materials are stored in locked filing cabinets at the HKU research laboratory. Only project staff have access to the study materials and data. All study materials and data will be shredded or otherwise destroyed 5 years after study completion. Deidentified data will be used in outcome data analysis by a study staff member who is blinded to participant group assignment.

Upon study completion, participants will retain their Fitbit Inspire 3 device as an incentive. All Fitbit devices were purchased from a local retail supplier in Hong Kong, with costs supported by the General Research Fund provided by the Hong Kong Research Grants Council (grant 17115422).

### Outcomes

#### Primary Outcome

MVPA, defined as the sum of “fairly active minutes” and “very active minutes” measured by the Fitbit device, is the primary outcome of this study. MVPA will be measured at baseline, immediately after the intervention, 12 months after the intervention, and at the 6-month follow-up.

#### Secondary Outcomes

All measurements of secondary outcomes will be conducted at baseline, immediately after the intervention, 12 months after the intervention, and at the 6-month follow-up. The secondary outcomes are presented in Textbox 1.

Secondary outcomes.
**Laboratory assessment variables**
BMI (kg/m^2^; derived from height and weight measurements)Systolic and diastolic blood pressure (mm Hg; measured using the Omron HEM-907 digital automatic blood pressure monitor)Resting heart rate (beats per minute; measured using the Omron HEM-907 digital automatic blood pressure monitor)Hand grip strength (kg; measured using the Jamar Hydraulic Hand Dynamometer [Fabrication Enterprises])
**Blood-based metabolic risk biomarkers**
Glycated hemoglobin (%)Total cholesterol (mmol/L)High-density lipoproteins (mmol/L)Low-density lipoproteins (mmol/L)Triglycerides (mmol/L)Fitbit device variablesSteps“Sedentary minutes” (minutes)“Lightly active minutes” (minutes)“Fairly active minutes” (minutes)“very active minutes” (minutes)“Activity calories” (kcal)Sleep time (minutes)
**Self-reported variables (assessed using a series of questionnaires)**
Physical activity and sitting timeFruit and vegetable consumptionSmoking statusPsychological variables to determine the effects of genetic risk communication

### Timing of Outcome Assessments

The time points for outcome measurements during the trial are presented in Table 1.

**Table 1 table1:** Schedule of assessments.

Assessments	Time points				
	Baseline	Immediately after the intervention	12 months after the intervention	6-month follow-up	After the follow-up
MVPA^a^ time (minutes)	✓	✓	✓		✓
Steps	✓	✓	✓		✓
Sedentary time (minutes)	✓	✓	✓		✓
Sleep time (minutes)	✓	✓	✓		✓
Lightly active time (minutes)	✓	✓	✓		✓
Fairly active time (minutes)	✓	✓	✓		✓
Very active time (minutes)	✓	✓	✓		✓
Activity calories (kcal)	✓	✓	✓		✓
Psychological variables of genetic risk communication	✓	✓	✓	✓	
PA^b^ and sitting time	✓	✓	✓	✓	
Fruit and vegetable consumption	✓	✓	✓	✓	
Smoking status	✓	✓	✓	✓	
Blood-based metabolic risk biomarkers	✓			✓	
Height (cm)	✓			✓	
Weight (kg)	✓			✓	
Handgrip strength (kg)	✓			✓	
Systolic and diastolic blood pressure (mm Hg)	✓			✓	
Resting heart rate (BPM^c^)	✓			✓	

^a^MVPA: moderate to vigorous physical activity.

^b^PA: physical activity.

^c^BPM: beats per minute.

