**Methods:**

In this parallel-group randomized controlled trial, 355 East Asians with overweight or obesity aged between 40 and 60 years are allocated to 1 of 3 groups: 1 control and 2 intervention groups. Blood samples are used for estimation of T2D genetic risk and tested for metabolic risk markers. T2D genetic risk is estimated based on 113 single nucleotide polymorphisms associated with T2D among East Asians using an established method. All 3 groups receive a Fitbit device. Both intervention groups will receive T2D genetic risk estimates along with lifestyle advice, but one of the intervention groups will receive additional Fitbit functions: step goal setting and prompt functions. The intervention materials are delivered weekly using WhatsApp and monthly via email. The primary outcome is MVPA time, which is objectively measured with the built-in accelerometer of the Fitbit Inspire 3 and will be assessed at baseline, immediately after the intervention, 12 months after the intervention, and at 6-month follow-up. Secondary outcomes include other parameters, such as sedentary time, BMI, systolic and diastolic blood pressure, 5 metabolic risk markers, handgrip strength, sleep, activity calories, self-reported physical activity, self-reported fruit and vegetable consumption, smoking status, and psychological variables.

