### Statistical Principles

We will present 95% CIs with adjusted marginal means to compare differences between groups at each measurement time point (baseline, immediately after the intervention, 12 months after the intervention, and 6-month follow-up). Results for the interaction term will also be presented. Pairwise between-group comparisons will be performed with Bonferroni adjustment. An overall level of statistical significance will be set at α=.05 before adjustment.

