### Analysis Populations

Primary outcome analysis will be conducted according to intention-to-treat principles. Participants with missing outcome data at the 6-month follow-up will be excluded from the analysis.

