### Analysis Methods

#### Primary Outcome

We will perform primary outcome analysis according to intention-to-treat principles using a series of linear mixed effects models with fixed effects for time, group, and group × time interactions for objectively measured MVPA time, with repeated measures for each participant. Models will be adjusted for potential confounders such as age, sex, and BMI. Adjusted marginal means with 95% CIs will also be presented to compare differences between study groups across all assessment time points.

The analysis will use a longitudinal data analysis model to examine patterns of differences across assessment time points, study groups, and group × time interactions. Results for the group × time interaction term will be included. In addition to the 4 assessment time points, the analysis will also be performed with time as a continuous variable across the study period. The effect modification will also be investigated according to the level of T2D genetic risk, which will be further categorized based on the average T2D genetic risk estimate and educational level of the sample (ie, between college and noncollege graduates). This post hoc categorization can enable us to examine the intervention effects within each group of genetic risk. To ensure fair random assignment of participants between the groups, we will examine between-group differences in the primary outcome data, using an ANOVA test or, if parametric assumptions are not met, a Kruskal-Wallis test.

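### Table 1 puts the last Fitbit measurement, MVPA included, in an undefined column after the 6-month follow-up, and its laboratory schedule disagrees with the text

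*SAP article*

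**What the plan says.** **Text on MVPA.** The primary outcome section states: "MVPA will be measured at baseline, immediately after the intervention, 12 months after the intervention, and at the 6-month follow-up". The abstract agrees: MVPA "will be assessed at baseline, immediately after the intervention, 12 months after the intervention, and at 6-month follow-up". Statistical Principles compares groups at the same four points: "baseline, immediately after the intervention, 12 months after the intervention, and 6-month follow-up". The analysis section counts them: "In addition to the 4 assessment time points, the analysis will also be performed with time as a continuous variable across the study period". Analysis Populations sets the exclusion rule: "Participants with missing outcome data at the 6-month follow-up will be excluded from the analysis". Sensitivity Analysis and Missing Data imputes at the 12-month and 6-month follow-up points, and Trial Objectives and Hypothesis claims an MVPA effect at the 6-month follow-up.

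**Table 1.** The table in Timing of Outcome Assessments has five time columns, not four. The fifth is headed "After the follow-up". The row "MVPA^a^ time (minutes" is ticked in columns 1, 2, 3 and 5 and is blank in column 4, the 6-month follow-up.

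**Text on the other outcomes.** The corresponding section states: "All measurements of secondary outcomes will be conducted at baseline, immediately after the intervention, 12 months after the intervention, and at the 6-month follow-up". Table 1 ticks the blood biomarkers, height, weight, grip strength, blood pressure and resting heart rate only at baseline and the 6-month follow-up.

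**The concern.** The last time point carries the claim that the effect on MVPA is sustained, and it alone determines who is dropped from the primary analysis. The table and the text name different columns for it, and no sentence says that the fifth column supplies the 6-month value. Two analysts could therefore build different analysis sets. One might require Fitbit data from the week after the visit. Another might read missing outcome data as non-attendance at the visit and keep a participant who attended but has no valid Fitbit week.

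The laboratory conflict is of a different kind. The stated schedule is wrong for six rows of Table 1. The analysis section then says that continuous secondary outcomes are handled much like the primary outcome, and also names ANOVA or Kruskal-Wallis for the biomarkers and laboratory variables, without saying how the baseline value enters.

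**Working it through.** **1. Table 1 row by row (18 rows).**

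| Rows | Baseline | Immediately after | 12 months after | 6-month follow-up | Fifth column |
|---|---|---|---|---|---|
| 8 Fitbit | ✓ | ✓ | ✓ | – | ✓ |
| 4 questionnaire | ✓ | ✓ | ✓ | ✓ | – |
| 6 laboratory | ✓ | – | – | ✓ | – |

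The rows sort cleanly by type of measurement: 8 + 4 + 6 = 18, with no exception. A table damaged in conversion would not do that. Safety Considerations gives a second check: it has the psychological questionnaires administered at all four time points, which matches their ticks in columns 1 to 4. So column 4 is one of the four time points, and the Fitbit tick sits outside it.

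**2. MVPA against the text.** MVPA has four ticks, and the text names four time points. Three ticks coincide; the fourth does not. Strengths and Limitations says that outcome data are collected over 7 days at each time point. Four ticks, four named points and a 7-day window together suggest that the fifth column is the week after the 6-month visit. That is an inference; the visible text does not state it.

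**3. How many participants the ambiguity could touch.** Sample Size expects 71 of 355 to drop out and, independently, 36 of 355 to lack Fitbit data: 355 − 71 − 36 = 248. Among the 355 − 71 = 284 who stay, 36/284 = 12.7% would lack Fitbit data. These are the people whose status depends on whether the exclusion rule refers to the visit or to the Fitbit week. The plan does not say at which time point the 36 are lost, so 36 is an indication of scale, not an estimate.

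**4. Sample size.** The arm means 80, 85 and 105 have mean 90, so their SD is √((100 + 25 + 225)/3) = 10.80, and f = 10.80/35 = 0.3086 (stated 0.3085). For the between-group test with m = 3 measures and ρ = 0.70, λ = N·f²·m/(1 + (m − 1)ρ). At N = 87 this is 87 × 0.3085² × 3/2.4 = 10.35, giving power 0.815. The minimum N is 85, or 87 in equal groups, so the plan's 87 reproduces. Nothing in this calculation uses the label of the last column.

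**5. Laboratory outcomes.** Each row has one baseline and one follow-up value. With baseline–follow-up correlation ρ, and relative to the variance of the follow-up value, the residual variance is 1 for ANOVA on follow-up alone, 2(1 − ρ) for ANOVA on change, and 1 − ρ² for ANCOVA. The documents give no ρ for laboratory measures. Borrowing the plan's 0.70 for MVPA as an assumption, the values are 1, 0.60 and 0.51. ANCOVA is below the first whenever ρ differs from 0 and below the second whenever ρ is below 1. The size of the gain depends on the true ρ.

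**The case against.** The best defence is that this is labelling. MVPA has the right number of ticks, every participant wears the device throughout the study, and outcome weeks last 7 days. Figure 1 (not shown) and the separately published protocol may also define the window. Most of this stands, and it is why the point is about reconciliation. It does not remove the conflict: table and text still name different time points for the primary outcome, and the exclusion rule follows the text.

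Three stronger readings are tempting and are not supported:

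- *A reader might infer that nobody has MVPA at the 6-month follow-up, so that the rule would exclude everyone.* The four ticks and the repeated reference to four MVPA time points make it far more likely that the fifth column is the 6-month value under another name.
- *A reader might infer that the primary-type model cannot be fitted to the laboratory data.* It can: with two measurements, time has two levels. The plan asks for a similar analysis, not a four-visit one, and also names ANOVA or Kruskal-Wallis for these variables.
- *A reader might infer that the clinic visit alters activity in the week that follows.* The documents offer no evidence of this. Table 1 gives one schedule for all arms, so no difference between arms is shown.

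**Conclusion.** The point holds as two inconsistencies within the article. First, the final time point of the primary outcome and of seven other Fitbit variables is unreconciled between Table 1 and the text. This concerns 8 of 8 Fitbit rows, and through the exclusion rule it leaves the primary analysis set open to more than one reading. Second, the statement that all secondary outcomes are measured four times is wrong for 6 of 6 laboratory rows, which have two measurements.

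No measurement is shown to be missing, no bias in an estimate is shown, and the sample size is unaffected. The reading of the fifth column as a 7-day window following the visit is an assumption; if Figure 1 or the protocol defines the column otherwise, that definition should be carried into the text. Baseline adjustment of the laboratory outcomes is an improvement available at no cost, not the repair of an analysis that would fail.

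**What to change.** 1. **MVPA window.** State in the primary outcome section, and in a footnote to Table 1, which single 7-day window supplies the 6-month MVPA value and where it lies relative to the 6-month visit. Rename or remove the fifth column accordingly, for all eight Fitbit rows.
2. **Missing-data rule.** Reword Analysis Populations so that missing outcome data means missing MVPA in that window, and use the same definition for the imputation.
3. **Laboratory schedule.** Correct the secondary outcomes section to say that the laboratory and blood measures are taken at baseline and the 6-month follow-up.
4. **Laboratory analysis.** Replace the unadjusted ANOVA or Kruskal-Wallis test for these measures with ANCOVA of the follow-up value on group and baseline, or the equivalent mixed model on the two time points.

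The cost is one table and a few sentences, with no new data. The article dates formal analysis from April 2025, so the clarification should carry a date and say whether it was made before outcome data were examined.

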### Timing of Final Statistical Analyses

All planned statistical analyses will be performed after the completion of the trial.

### Statistical Principles

We will present 95% CIs with adjusted marginal means to compare differences between groups at each measurement time point (baseline, immediately after the intervention, 12 months after the intervention, and 6-month follow-up). Results for the interaction term will also be presented. Pairwise between-group comparisons will be performed with Bonferroni adjustment. An overall level of statistical significance will be set at α=.05 before adjustment.

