### Sample Size

To ensure sufficient statistical power, we intend to recruit 355 East Asian participants with overweight or obesity. An oversampling strategy has been adopted, with 35.1% (87/248) of the full sample consisting of individuals at a higher genetic risk for T2D. The required number of participants (n=87) for subsample analysis was based on the desired medium effect size (*F*=0.3085), derived from a 3-group comparison. The control group’s average wearable device–measured MVPA time was 80 (SD 35) min/d. The intervention group receiving genetic risk information alone (intervention arm 1) demonstrated minimal changes (85 min/d), while the intervention group receiving combined genetic risk information and wearable device functions (intervention arm 2) was expected to show a difference of approximately 23% in MVPA time (105 min/d; [(105 − 85) / 85 × 100%], corresponding to a difference of 23% in MVPA time compared to previous Fitbit interventions) [26].

Our sample size calculation assumed an α level of 5%, a power of 80%, and a correlation of 0.70 among 3 repeated measures. A total of 355 participants are recruited to ensure the inclusion of an analysis sample of 248, while factoring in an expected attrition rate of 20% (71/355) and an anticipated Fitbit data missing rate of 10.1% (36/355), independent of attrition, considering instances of insufficient battery life or device loss.

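### The Bonferroni adjustment of the three arm comparisons is valid, but a step-down rule over the same family would recover power at the same familywise error

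*SAP article*

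**What the plan says.** Under Framework, the SAP article names all three pairs: "Each intervention group (intervention arm 1 and intervention arm 2) will be compared separately with the control group and with each other". Under Statistical Principles it states "Pairwise between-group comparisons will be performed with Bonferroni adjustment" and "An overall level of statistical significance will be set at α=.05 before adjustment". The same section adds "We will present 95% CIs with adjusted marginal means to compare differences between groups at each measurement time point", and lists baseline and three later assessments.

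The article does not say whether the Bonferroni family is the three pairs within a visit or all pairs at all visits. The interaction term is to be reported, but no pairwise test depends on it or on any joint test of the arms.

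Under Sample Size the calculation rests on a joint test: "The required number of participants (n=87) for subsample analysis was based on the desired medium effect size (*F*=0.3085), derived from a 3-group comparison".

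**The concern.** With three arms, Bonferroni over the pairs tests each at 0.05/3 = 1.67%. Three pairwise null hypotheses are logically linked: if two are true, so is the third. Once one pair is known to differ, at most one of the other two nulls can be true, and dividing alpha by three for those is stricter than 5% familywise control requires.

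The unused error is largest near the trial's own hypothesis, in which arm 1 barely differs from control and arm 2 differs from both. If arm 1 equals control exactly, only one null is true and Bonferroni spends 1.7% per visit on it. The cost falls mainly on arm 2 versus arm 1, the contrast that isolates the added wearable functions and so bears on the second trial objective.

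**Working it through.** **Inputs (Sample Size and Randomization).** Control "MVPA time was 80 (SD 35) min/d"; arm 1 at 85 min/d; arm 2 "was expected to show a difference of approximately 23% in MVPA time (105 min/d"; alpha 5%, power 80%, correlation 0.70 among 3 repeated measures; 87 in the subsample (29 per arm); 248 analysed (83, 83 and 82); 1:1:1 allocation. Assumed: two-sided tests, normal outcomes, common SD, and a Bonferroni family of three pairs within a visit.

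**The plan's own figure.** The mean of 80, 85 and 105 is 90. The SD of the means is √[(100 + 25 + 225)/3] = 10.80, and f = 10.80/35 = 0.3086 (stated 0.3085). For the joint test on 3 repeated measures, λ = f²·N·m/[1 + (m − 1)ρ] = 0.0952 × 87 × 3/2.4 = 10.4. On 2 and 84 df this gives 81.5% power. So n = 87 reproduces, for the joint three-group test.

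**Pairwise power under Bonferroni (normal approximation, one visit).** SE = 35·√(2/n).
- 29 per arm: SE = 9.19; 20/9.19 = 2.18; power = Φ(2.18 − 2.39) ≈ 41%.
- 83 per arm: SE = 5.43; 20/5.43 = 3.68; power = Φ(3.68 − 2.39) ≈ 90%.

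**The alternatives.** Holm tests the smallest p-value at 0.05/3, the next at 0.05/2 and the last at 0.05. The three-arm step-down rule tests the smallest at 0.05/3 and, if that is significant, the other two at 0.05. It is valid because of the logical link between the three nulls. Both share Bonferroni's first step and are no stricter afterwards, so neither can lose a rejection that Bonferroni makes.

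**Simulated power, arm 2 versus arm 1** (pooled variance, 400,000 runs). The SD is 35 for one visit, 35·√(2.4/3) = 31.3 for the mean of 3 visits, and 35·√(1 − 0.7²) = 25.0 with baseline adjustment.

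| N | Analysis | Bonferroni | Holm | Step-down |
|---|---|---|---|---|
| 248 | one visit | 89.6% | 92.9% | 95.3% |
| 248 | mean of 3 visits | 95.4% | 97.3% | 98.3% |
| 248 | baseline-adjusted | 99.7% | 99.9% | 99.9% |
| 87 | one visit | 39.9% | 44.3% | 51.0% |
| 87 | mean of 3 visits | 49.8% | 54.9% | 62.1% |
| 87 | baseline-adjusted | 72.5% | 77.7% | 83.4% |

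For arm 2 versus control at one visit there is less to gain. The 248 go from 98.5% to 98.8% (Holm) or 99.0% (step-down), and the 87 from 61.1% to 62.9% or 65.5%.

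**Familywise error within a visit** (1,000,000 runs). Under the global null, Bonferroni and the step-down rule both give 4.4%, since they share the first step. With two arms equal and the third different, Bonferroni gives 1.7% and the step-down rule at most 5.0%.

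**Error across three post-baseline visits, correlation 0.70.** Under the global null, the chance of any false finding is already about 10% if Bonferroni covers only the pairs within a visit. At means 80/80/105 with 83 per arm, the chance of any false arm 1 versus control claim is 3.9% with Bonferroni. It is 11.0% with a joint test at 5% followed by unadjusted pairs. The step-down rule would be close to the latter: with one arm shifted by 20 min/d, the two rules have nearly the same error per visit at this size (4.99% and 5.00%).

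**The case against.** The plan makes no mistake here. Bonferroni controls the familywise error, and in the 248 it already gives arm 2 versus arm 1 about 90% power, above the 80% target. That stands, and it limits the point to efficiency.

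A reader might infer three stronger things that the documents do not support.
- **That the trial forgoes up to 14 points of power.** A gain that large (39.9% to 53.4%, or 13.5 points) arises only in the 87-person subsample, and only with a joint test at 5% followed by unadjusted pairs. In the 248 the same rule gains 5.8 points at one visit.
- **That this gated rule dominates Bonferroni.** It does not. In about 0.4% of simulated trials at 29 per arm, Bonferroni rejects and the joint test blocks the claim. Only Holm and the step-down rule keep every Bonferroni rejection.
- **That the plan fixes each pair at 1.67%.** It never defines the family. If pairs and visits were both meant, the power loss is larger, but a rule applied visit by visit would not be an equal replacement.

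Two costs also stand. Without a rule across visits, Bonferroni's spare error gives some protection, and removing it visit by visit raises false claims for genetic-risk communication alone from about 4% to about 11%. Bonferroni also has matching simultaneous intervals, which the step-down rules lack. An unadjusted interval can therefore exclude zero where the adjusted test does not reject.

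**Conclusion.** The adjustment is valid but gives up some power. If the family is three pairs at one visit and the SD is 35, a step-down rule gains about 3 points (Holm) or 6 points (three-arm rule) for arm 2 versus arm 1 in the 248. The corresponding gains in the high-risk subsample are about 4 or 11 points. In the 248 they fall to about 0 to 3 points if visits are averaged or baseline is adjusted for at correlation 0.70. All of this rests on the planning means and SD.

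The gain comes at the same nominal familywise level only if the rule covers the family Bonferroni was meant to cover. A rule confined to each visit does not control error over several visits. This is a worthwhile low-cost improvement and not a flaw that threatens the trial's conclusions.

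**What to change.** In Statistical Principles, define the family and replace the Bonferroni sentence with one of the following:
- **One primary time point:** name it, and test the three pairs there with the step-down rule (smallest p-value at 0.05/3; if significant, the other two at 0.05). Comparisons at other visits are then supportive.
- **All pairs at all visits:** apply Holm over that whole family.

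Add that the 95% confidence intervals are unadjusted for multiplicity and may differ from the adjusted tests.

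The cost is a sentence or two and the loss of matching simultaneous intervals; no further data are needed. The article places formal analysis from April 2025. The change should therefore be dated and made before anyone sees unblinded comparisons. If that point has passed, keep Bonferroni as the planned analysis and report any step-down result as post hoc.
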